## Background

Automated insulin delivery (AID) systems are globally recognised as the gold standard for managing glucose levels in people with type 1 diabetes (T1D) [1, 2]. These systems link an insulin pump, continuous glucose monitor (CGM) and computer algorithm to semi-automate insulin delivery. AID systems have been shown to greatly improve glycaemic outcomes [3]. For example, in a randomised controlled trial of children and youth aged 7 to 25 years with above-target glycemia, HbA1c decreased by 2.5% (95% CI −3.1 to 1.8 [−27mmol/mol, 95% CI −34 to −20] *p* < 0.001) and time in range (TIR) increased by 35% (95% CI 28 to 41%) after using AID for 13-weeks, compared to the control group (multiple daily injections or continuous subcutaneous insulin infusion) [4].

Despite this evidence, in Aotearoa New Zealand (herein referred to as NZ) and worldwide, access to these advanced diabetes technologies is slow and inequitable [5–7]. Until recently in NZ, the main barriers to access included the lack of publicly funded CGM and restrictive eligibility criteria for insulin pump funding and consumables particularly for adults, people from low socioeconomic backgrounds, or ethnic minorities [5] with similar trends observed worldwide [8]. However, in October 2024, funding in New Zealand was expanded to include CGM and pumps for all people with type 1 and related forms of diabetes, enabling broader use of AID systems. Despite advances in technology and liberalisation of funding, many barriers to access remain. Historical treatment guidelines prioritised those who had more in-target glycemia and diabetes management skills [9, 10], effectively gatekeeping this technology from individuals who experience the greatest absolute benefits. Furthermore, workforce constraints, and sometimes overly complicated training and support pathways remain key barriers [11, 12] with evidence from the UK highlighting funded practitioner time as a key barrier for supporting individuals to use this technology [13]. Now more than ever, there is an urgent need to provide efficient and equitable access to AID for the thousands of individuals estimated to seek this technology in the coming years.

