### Outcomes

The primary outcome of this study is to assess the implementation effectiveness of the Hub. Secondary outcomes of this study include intervention effectiveness, safety and acceptability, psychosocial measures, nutrition education effectiveness, cost-effectiveness and clinical staff self-efficacy and intervention acceptability.

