#### Implementation effectiveness

Implementation effectiveness of the Hub, at facilitating AID starts and addressing inequities in care, will be assessed by determining the number and characteristics of people who are referred and enrolled by the Hub, and the time to discharge on AID. Counts of AID starts will be compared by provider (Hub versus all others) and over time (weekly from 12 months prior to Hub implementation until study end). Incidence proportions of new AID starts, and prevalence for overall AID usage, will be estimated nationally and by region for priority populations; Māori, Pacific, those living in rural areas, and those living in areas of highest socioeconomic deprivation as measured by the NZ deprivation index [37].

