### Statistical analysis

Pharmac, NZs pharmaceutical funding agency, estimates there are 18,000 to 21,000 people with pancreatic insufficiency (mostly T1D) living in NZ who would be eligible for funded CGM [11], of whom 85–90% were not using AID in 2023. We believe the Hub will facilitate approximately 500 new AID starts per year (provided by 2.4 full time equivalent clinical staff, per year).

A sample size of 500 or more participants will provide > 90% power, with a two-sided alpha of 0.05, to detect small changes in continuous outcomes (effect sizes ≥ 0.15) and estimate binary outcomes to within +/- 5%.

Numbers of people referred to the Hub, enrolled, and started on AID will be tabulated by the key demographic and clinical variables required for calculation of the prioritisation score as listed under Sect. 2.5.1.

Incidence proportions, stratified by region and priority subpopulations, will be calculated as the number of AID starts divided by the number of eligible people not on AID as estimated from national administrative datasets. For comparisons with other providers, an individual will be considered to have started on AID on the date they are first dispensed a subsidised pump as recorded by Health New Zealand.

Interrupted time series analysis will be used to investigate the impact that the Hub has on the rate of new AID starts nationally, and by region, Absolute numbers and incidence proportions of new AID starts will be calculated for consecutive time periods and displayed graphically. Generalised linear (Poisson) regression models will be used to estimate changes in the in the numbers and incidence of new AID starts before versus after deployment of the Hub. Differences between regions, such as workforce capacity, may be explored in models to identify facilitators and barriers to AID uptake.

Intervention effectiveness will be confirmed by descriptively summarising changes in Hub participants’ HbA1c and CGM metrics before versus after starting on AID.

National laboratory and CGM data is not available for those not enrolled in the study.

Incidence rates of adverse events will be calculated for study participants after AID start and compared to control populations utilising generalised linear regression models, adjusting for demographic factors (age, gender, ethnicity, NZ deprivation index). Controls will included study participants prior to AID start and non-study people with type one diabetes who have and have not started on AID.

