This study addresses an urgent and growing health need in NZ, and provides a framework for the roll out of a sustainable and equitable model of care that complements existing services. We view this as the future of mainstream diabetes technology training and support, especially during this period of peak uptake. Establishing a precedent and evidence for this sort of nationally delivered health care model is vital for NZ, and this work could be adapted for management of other chronic conditions.

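### As specified, the interrupted time series does not separate the Hub from the October 2024 funding expansion, so its Hub effect may be biased in either direction

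*Protocol article*

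**What the plan says.** Under Outcomes: "The primary outcome of this study is to assess the implementation effectiveness of the Hub". The Implementation effectiveness section lists several components. Some are descriptive: numbers and characteristics of people referred and enrolled, and time to discharge. Another is comparative: "Counts of AID starts will be compared by provider (Hub versus all others) and over time", with the time axis running "weekly from 12 months prior to Hub implementation until study end".

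The Statistical analysis section gives this comparison a causal purpose: "Interrupted time series analysis will be used to investigate the impact that the Hub has on the rate of new AID starts nationally", and also by region. The model is named next: "Generalised linear (Poisson) regression models will be used to estimate changes in the" "numbers and incidence of new AID starts before versus after deployment of the Hub". For comparisons with other providers, a start is dated by the first dispensing of a subsidised pump.

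Two other statements cover the same period. The Background says that "in October 2024, funding in New Zealand was expanded to include CGM and pumps for all people with type 1" and related forms of diabetes, after a time of restrictive pump funding. The Discussion says the model of care is needed "especially during this period of peak uptake".

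The article does not give the Hub start date. The analysis text does not mention the funding change, and it does not describe trend terms, dispersion or autocorrelation.

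**The concern.** An interrupted time series attributes to the intervention whatever changed at the interruption and is not explained by the earlier course of the series. Here a second national event, the funding expansion, may fall inside or close to the 12-month baseline. It acts on the outcome directly, because a count of subsidised pumps depends on who is entitled to one. The pool waiting to start was also large: the article's figures imply 18,000 × 0.85 = 15,300 to 21,000 × 0.90 = 18,900 eligible people not on AID in 2023.

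Growth driven by funding could therefore be reported as an effect of the Hub. If one straight pre-Hub trend is fitted through a funding jump, a fall could be reported that did not happen. The regional analysis does not solve this by itself, because the funding change reached every region at once.

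**Working it through.** **The plan's own figure.** The article gives no figure for the time series. Its power statement concerns within-participant change, and it reproduces: Φ(0.15 × √500 − 1.96) = Φ(1.394) = 91.8%, and 1.96 × √(0.25/500) = 4.4 percentage points. It says nothing about whether the time series can isolate the Hub.

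**Inputs from the article.** Weekly data; 12 months (52 weeks) before the Hub; funding change in October 2024; about 500 Hub starts a year, which is 500/52 = 9.6 a week.

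**Assumptions, because the article does not give them.** 52 weeks after the Hub; funding multiplies background starts by m = 1.25, 1.5 or 2; the change begins g = 13, 26, 39 or 52 weeks before the Hub; it acts at once or as a ramp over 26 or 52 weeks; 30 starts a week before funding; true Hub ratio 1.00. The 30 a week cancels from the before/after ratio and matters only for significance rates.

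**Immediate step, before/after model.** The expected ratio is R = 52m / [(52 − g) + g × m].

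| m | g = 13 | g = 26 | g = 39 | g = 52 |
|---|---|---|---|---|
| 1.25 | 65/55.25 = 1.18 | 65/58.5 = 1.11 | 65/61.75 = 1.05 | 1.00 |
| 1.5 | 78/58.5 = 1.33 | 78/65 = 1.20 | 78/71.5 = 1.09 | 1.00 |
| 2 | 104/65 = 1.60 | 104/78 = 1.33 | 104/91 = 1.14 | 1.00 |

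Simulation (100 replicates per scenario) agrees to within 0.01. For g = 13 to 39 it finds a significant Hub effect in 36% to 100% of runs.

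**Ramp, before/after model.** Take m = 2 and a 26-week ramp starting 13 weeks before the Hub.
- Baseline mean: (39 × 1 + 13 × 1.25)/52 = 1.0625.
- Post-Hub mean: (13 × 1.75 + 39 × 2)/52 = 1.9375.
- Ratio: 1.9375/1.0625 = 1.82; the simulation gives 1.84.

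**Simulated ratios by model (true value 1.00).**

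| Scenario | Before/after | Segmented, no funding term | Segmented plus funding step |
|---|---|---|---|
| Step, g = 13 to 39 | 1.05 to 1.60 | 0.82 to 1.05 | 0.99 to 1.01 |
| Ramp, g = 13 to 39 | 1.12 to 1.84 | 0.88 to 1.47 | 0.87 to 1.44 |
| Step, g = 52 | 0.99 to 1.00 | 0.99 to 1.00 | not fitted |
| Ramp, g = 52 | 1.06 to 1.39 | 0.85 to 1.00 | not fitted |

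The segmented model without a funding term errs in both directions. A doubling at g = 26 gives 0.82, significant in 97% of runs. A 26-week ramp to a doubling from g = 13 gives 1.47, significant in all runs. A simple funding step repairs a step but not a ramp.

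**Scale.** The Hub's planned 9.6 a week on an assumed 30 is 9.6/30 = 32%. A 1.5-fold funding step 13 weeks before the Hub gives 1.33 with no Hub effect, about the same size.

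**Secondary check, error model.** With no funding change and an assumed 50 starts a week (400 replicates), plain Poisson errors at a nominal 5% reject as follows.
- Dispersion 1: 4% to 6%.
- Dispersion 2: 16% to 19% (analytic: 2 × [1 − Φ(1.96/√2)] = 17%).
- Dispersion 3: 19% to 24% (analytic 26%).
- Dispersion 2 or 3 with lag-1 correlation 0.4: 24% to 44%.

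Pearson scaling restores 3% to 7% without autocorrelation, but leaves 9% to 16% with it.

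**The case against.** The strongest reply is that the article names an interrupted time series, which usually carries trend terms, and that covariates are commonly left to an analysis plan not shown here. On that view, silence on funding does not exclude it, and the largest before/after ratios belong to a model the authors may not intend. This is fair. But segmented models without a funding term also err (0.82 to 1.47), and the 12-month window is stated, not left open. Within that window a simple funding step leaves 0.87 to 1.44 under a ramp, so the window limits what a later plan can recover.

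A second reply is that the weekly Hub-versus-others split already supplies a comparison series. It helps, but it is planned as a comparison of counts. It is also not a clean control: Hub staff are seconded from existing services (Background) and patients may be referred from any provider (Recruitment), so the Hub can displace starts elsewhere.

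Third, the check covers counts only. The article also models incidence among eligible people not on AID. If eligibility followed funding, that denominator moved too, and the bias in incidence could differ.

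A reader might infer that the two effects can never be separated, or that plain Poisson intervals are certainly too narrow. The documents support neither. The Hub date and the shape of uptake are not given, and a settled background leaves a clean baseline. The article reports no weekly counts and does not say that dispersion will be ignored, so the error-model point is conditional.

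**Conclusion.** The concern holds in a conditional form. As written, the time series does not separate the Hub from the funding expansion. Its Hub estimate is biased if the Hub began less than about 12 months after October 2024, or if uptake after funding rose gradually. With funding effects of 1.25- to 2-fold beginning 13 to 39 weeks before the Hub and no Hub effect, the ratio is about 1.05 to 1.84 before/after, or about 0.82 to 1.47 segmented without a funding term. If uptake had settled before the baseline began, the bias is near zero. The funding multipliers, timing and ramp shapes are assumptions.

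It would be wrong to conclude that the error always favours the Hub, since a segmented model can show a false harm. It would also be wrong to conclude that the whole primary outcome fails. Referral and enrolment numbers, participant characteristics and time to discharge are descriptive and unaffected. The time series is nevertheless the component meant to support a statement about the Hub's impact, so it should be corrected before analysis.

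**What to change.** 1. State the Hub start date relative to October 2024.
2. Extend the pre-Hub dispensing series to at least 12 months before October 2024.
3. Fit separate level and slope terms at the funding change and at Hub deployment, allowing the funding effect to be gradual.
4. Model total starts and non-Hub starts as separate series, so that displaced starts are visible.
5. As a secondary change, use quasi-Poisson or negative binomial errors with autocorrelation-robust or AR(1) standard errors, and report the interval from that model.

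The cost is plan wording and a longer administrative extract. The interval for the Hub effect will be wider. Weeks before October 2024 were recorded under narrower pump-funding criteria, so the funding terms must absorb a change in what the count captures. The extended model was not simulated here. A slow ramp may remain only partly separable, and this should be stated as a limitation.

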#### Telehealth consultation

Participants and their whānau (families) will be invited to attend a telehealth consultation with a staff member of the Hub. During the consultation, individuals will have the opportunity to discuss current commercial AID options in NZ, which at the time of this protocol development includes the Control-IQ system with the Tandem t: slim X2 insulin pump (Tandem Diabetes Care Incorporated, California, USA) and the CamAPS system (CamDiab Limited, Cambridge, England) with the mylife Ypsopump (Ypsomed Holding AG, Burgdorf, Switzerland). Other systems are commercially available in NZ but funded access is restricted so beyond the scope of this model of care. Following initial consultation, participants will select their preferred AID system including the compatible CGM. Two weeks of CGM data prior to AID commencement will be used as baseline glycaemic data. Participants will be provided with a pump start guide that includes information about starting AID, and will be used by clinical staff during education and participant follow up.

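### The adverse-event model names no calendar-time term, so any national trend in admissions enters the comparison of participants' time on AID with their own earlier time

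*Protocol article*

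**What the plan says.** The safety comparison is set out in the last paragraph of the Statistical analysis section: "Incidence rates of adverse events will be calculated for study participants after AID start and compared to control populations". The method is generalised linear regression, "adjusting for demographic factors (age, gender, ethnicity, NZ deprivation index". The comparators are three: "Controls will included study participants prior to AID start and non-study people with type one diabetes who have and have not started on AID".

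The Intervention safety section lists the events (death, and hospital admissions for DKA, severe hypoglycaemia and hyperglycaemia) and says that control rates come from national Health New Zealand data. Neither section gives the calendar window of the control person-time. The 12-month look-back under Implementation effectiveness applies to counts of AID starts.

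Two statements in the Background bear on this. Funding changed nationally: "in October 2024, funding in New Zealand was expanded to include CGM and pumps for all people with type 1". And CGM is part of every AID system: "These systems link an insulin pump, continuous glucose monitor (CGM) and computer algorithm to semi-automate insulin delivery". Under Telehealth consultation, participants are on CGM for at least a short run-in: "Two weeks of CGM data prior to AID commencement will be used as baseline glycaemic data".

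**The concern.** For any one participant, time after AID start is later than time before it. If admission rates were changing nationally for reasons unrelated to the Hub, a before/after rate ratio without a period term credits that change to starting AID through the Hub. The four named covariates cannot help: within a person, gender, ethnicity and deprivation are essentially fixed, and age moves only by the gap between the two periods.

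A national trend is a realistic possibility, because the plan itself describes a step change in access to CGM and pumps in October 2024. Safety is part of the first objective. If rates were falling, a real increase in admissions after remotely supported starts could be offset in this contrast and read as no change. The plan treats time carefully elsewhere: AID starts are analysed as an interrupted time series. The safety model has no counterpart to that.

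**Working it through.** **The plan's own figures.** The document gives no adverse-event rate, rate ratio or power for safety. Its only design figures reproduce on a one-sample or paired reading: power = Φ(0.15 × √500 − 1.96) = Φ(1.394) = 0.918, and precision = 1.96 × √(0.25/500) = 4.4 percentage points. Neither bears on this point.

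**The three contrasts differ.**

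| Control group | Is control time earlier? | Is it less often on CGM? | Other unadjusted differences |
|---|---|---|---|
| Participants before AID start | Yes, for each person | Possibly; only the last two weeks are known to be on CGM | Selection on recent severe hypoglycaemia (regression to the mean, favours the Hub) |
| Non-study, on AID | Not stated | No, CGM is part of AID | Prioritisation on HbA1c, severe hypoglycaemia and complications (disfavours the Hub) |
| Non-study, not on AID | Not stated | Plausible, not documented | As in the row above |

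**Trend in the before/after contrast.** Let t be the national event rate over the calendar time after AID start, divided by that over the time before. With no period term, apparent ratio = true ratio × t. The document gives nothing from which to estimate t.

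**Illustration for CGM alone.** Let c be the rate ratio for events on CGM versus off it, and f the share of control person-time without CGM. Time on AID is all CGM time. If AID adds nothing beyond CGM, the apparent ratio is c / (f + (1 − f)c). Both inputs are assumptions.

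| | f = 0.2 | f = 0.5 | f = 0.8 |
|---|---|---|---|
| c = 0.6 | 0.6/0.68 = 0.88 | 0.6/0.80 = 0.75 | 0.6/0.92 = 0.65 |
| c = 0.7 | 0.7/0.76 = 0.92 | 0.7/0.85 = 0.82 | 0.7/0.94 = 0.74 |
| c = 0.9 | 0.9/0.92 = 0.98 | 0.9/0.95 = 0.95 | 0.9/0.98 = 0.92 |

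At f = 0, the case of non-study AID users, the ratio is 1.00. A true harmful ratio that would be brought back to 1 is the reciprocal: 1/0.82 = 1.2 in the middle cell, 1/0.65 = 1.5 in the most extreme.

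These values overstate the bias to the extent that participants begin CGM as part of starting AID through the Hub. That part belongs to the package. Only the CGM uptake that would have happened anyway is confounding, and that is the part a period term addresses.

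**The opposing force against non-study controls.** Let h be the excess baseline risk of Hub participants left unadjusted. The apparent ratio becomes h × c / (f + (1 − f)c), which equals 1 when h = (f + (1 − f)c)/c. At f = 0.5 this is 0.80/0.6 = 1.33, 0.85/0.7 = 1.21 and 0.95/0.9 = 1.06 for c = 0.6, 0.7 and 0.9. Any larger excess turns the ratio against the Hub. The document gives no value of h, but Table 2 prioritises on several strong risk factors, so an h in or above this range cannot be ruled out.

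**The case against.** A reader might infer that all control time is earlier and less often on CGM, and that every safety ratio therefore flatters the Hub. The document does not support that.

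- Non-study AID users are on CGM by definition, and nothing shows that their time is earlier. This contrast asks most directly whether a Hub start is as safe as a start elsewhere, and the plan already includes it.
- Against non-study people not on AID, the unadjusted prioritisation factors push the other way, so the net direction is indeterminate.
- The Hub's start date and the window for safety person-time are not given. That control time straddles October 2024 is an inference, and non-study control time may be fully concurrent.
- A CGM covariate is not a plain correction. It changes the question from AID versus no AID to AID beyond CGM. The Statistical analysis section also says that national laboratory and CGM data do not exist for people outside the study; that may mean glucose readings and not dispensing, but linkage cannot be assumed.

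All four stand, and they confine the point. It can also be said that the covariate list is not called exhaustive and that a statistical analysis plan may define the windows. That is fair for the windows. The adjustment set, however, is spelled out in the article, and so is the use of earlier own time as a control. Followed as written, the model leaves calendar time uncontrolled in the before/after contrast.

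**Conclusion.** The point holds for one contrast. In the comparison of participants after AID start with their own time before it, the stated model confounds starting AID through the Hub with any national change in admission rates. A downward trend would favour the Hub; an upward one would do the reverse. CGM use does not bias the comparison with non-study AID users, and no net direction can be claimed against non-study people not on AID.

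The size is not computable from the document. The range of 0.65 to 0.98 is an illustration of the CGM component alone. It rests on an assumed CGM rate ratio of 0.6 to 0.9, an assumed 20 to 80% of control time without CGM, and no other confounding. Safety is a secondary outcome but part of the first objective, and the correction is cheap, so it should be made.

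**What to change.** 1. Add calendar quarter to the adverse-event model in the Statistical analysis section. Fit it with concurrent non-study person-time included, so that the period effect is estimated from people whose AID status is not changing at the same moment.
2. State the calendar window for each control group. Restrict control person-time to the window of Hub follow-up, or at least to after October 2024.
3. Report the three contrasts separately, and say that the before/after contrast remains open to regression to the mean, which a period term does not remove.
4. Optionally, if CGM dispensing can be linked, add a contrast with time on CGM without AID as a secondary, separately labelled estimand.

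Steps 1 to 3 need only dated events and dated pump dispensing, which the planned national data should already provide. The cost is less control person-time, mainly participants' own time before AID start, and so wider intervals for rare events. The period term also assumes that the trend in non-study people represents the one that participants would have followed; this should be stated.

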## Methods

### Trial conduct

#### Study design

This is a quasi-experimental, single-arm study which will assess a new model of AID health care delivery in NZ. The new model of health care will be the remote Hub which will be deployed to provide prioritised national AID set up and support, before transferring participants back to their usual care teams after a maximum of 12 weeks (See Fig. 1 for summary of study design). The duration from referral to enrolment may vary depending on participants prioritisation score (outlined below in Sect. 2.3.2).

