#### Prioritisation score

Data collected from the referral form will be used to calculate a prioritisation score (Table 2). Given the substantial waiting lists for AID access across NZ, the prioritisation score is designed to ensure current inequities in access to AID are addressed and those who may benefit the most are prioritised.

**Table 2 Tab2:** Study prioritisation framework

Priority items:	Potential Score
Māori and/or Pacific ethnicity	2 points
HbA1c > 86 mmol/mol (10%) ^1^	2 points
Living rurally ^2^	1 point
HbA1c 58–85 mmol/mol (7.5 to 10%)	1 point
Severe hypoglycaemia in last 2 years	1 point
Age < 25 years ^3^	1 point
Known diabetes complications	1 point
Occupational requirement (e.g. driver/shift worker)	1 point
**Potential total**:	**10 points**

^1^HbA1c target is < 53mmol/mol (the above target those who are less healthy)

^2^Rurality defined using participants home address and the Geographical Classification of Health [35]

^3^Younger age – due to longer potential life with diabetes and risk of complication over time

Based on assessment of the prioritisation score, and study capacity, individuals will be invited to enrol in the Hub via email or phone.

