#### Intervention safety

Intervention safety will be assessed by the occurrence of serious adverse events (SAEs) including death and hospital admissions for diabetic ketoacidosis (DKA), severe hypoglycaemia (defined as coma or convulsion requiring assistance from others) and hyperglycaemia. Participants will be instructed to notify study staff immediately in the event of any SAE related to the study, as outlined above. Incidence will be calculated for study participants and compared to controls utilising national data captured by Health New Zealand.

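### The before/after safety contrast is selected upward for severe hypoglycaemia and cannot be made for death; the non-study contrast leaves most priority-score items unadjusted

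*Protocol article*

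**What the plan says.** Four parts of the protocol article bear on this.

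- **Events.** Intervention safety defines the outcome as "serious adverse events (SAEs) including death and hospital admissions for diabetic ketoacidosis (DKA), severe hypoglycaemia", and also admissions for hyperglycaemia. Severe hypoglycaemia is defined there by coma or convulsion needing help.
- **Controls and model.** Statistical analysis names the comparators: "Controls will included study participants prior to AID start and non-study people with type one diabetes who have and have not started on AID". Rates are compared in generalised linear models, "adjusting for demographic factors (age, gender, ethnicity, NZ deprivation index").
- **Selection.** Table 2 under Prioritisation score gives one point for "Severe hypoglycaemia in last 2 years". Other points go to ethnicity, HbA1c, rurality, age, complications and occupation. Invitation depends on score and study capacity. Study population says the score sets how quickly people get access.
- **Design.** Study design states: "This is a quasi-experimental, single-arm study". There is no concurrent randomised group against which to read safety.

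The article does not say how long the pre-AID control period is. It does not exempt any event type from the own-control comparison.

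**The concern.** Two features of the own-control contrast are built in before any AID effect.

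First, a person who had severe hypoglycaemia before referral is more likely to be enrolled, or is enrolled sooner. Enrolled people therefore carry an excess of such events in their pre-AID time. That excess does not carry over in full to the period after start, so the rate falls by regression to the mean. Adjusting for demographic factors does not remove this, because the selection acts on the event itself.

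Second, a participant must be alive at AID start, so the pre-AID period can contain no death.

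The two act in opposite directions: severe hypoglycaemia tends to look better after AID, and death can only look worse. A pooled SAE rate would mix them.

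The comparison with non-study people does not share these two faults, but it has confounding by the Hub's own selection criteria. Safety is part of the first objective and the study has one arm, so these contrasts are its comparative safety evidence.

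**Working it through.** **The plan's own figure.** Statistical analysis states: "A sample size of 500 or more participants will provide > 90% power, with a two-sided alpha of 0.05", for standardised effects of at least 0.15. A single-group before/after calculation gives Φ(0.15×√500 − 1.96) = 0.918. The worst-case 95% half-width for a proportion is 1.96×√(0.25/500) = 0.044. Both statements reproduce and are not at issue, but they do not cover the adverse-event rate comparison.

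**Severe hypoglycaemia, closed form.** The inputs below are assumptions, except the two-year look-back from Table 2.

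- Each person's rate is gamma distributed with mean m per year and shape a, and is unchanged by AID.
- People with any event in the two years are enrolled k times as often as the rest.
- The pre-AID period lies within the look-back, and the scored and counted events coincide.

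With enrolment weight w (k after an event, otherwise 1):

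- pre-AID rate = k·m / E[w]
- post-AID rate = (k·m − (k−1)·E[λe^(−2λ)]) / E[w]
- E[λe^(−2λ)] = m·(a/(a+2m))^(a+1)
- ratio after/before = 1 − ((k−1)/k)·(a/(a+2m))^(a+1)

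| m | a | k | Ratio with no AID effect |
|---|---|---|---|
| 0.05 | 2 | 3 | 1 − 0.667×0.864 = 0.42 |
| 0.10 | 1 | 2 | 1 − 0.500×0.694 = 0.65 |
| 0.15 | 0.5 | 1.5 | 1 − 0.333×0.494 = 0.84 |
| any | any | 1 | 1.00 |

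**Severe hypoglycaemia, selection by score.** A simulation of 2,000,000 people per scenario assigned Table 2 points with assumed, independent prevalences. Rates were 0.02 to 0.10 per year and frailty variance 0 to 5. The highest scorers were enrolled, and one pre-AID year inside the look-back was compared with the true rate afterwards.

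| Share enrolled | Ratio with no AID effect |
|---|---|
| everyone | 0.99 to 1.01 |
| top 50% | 0.66 to 0.84 |
| top 25% | 0.52 to 0.78 |
| top 10% | 0.42 to 0.73 |

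**Is selection plausible?** Statistical analysis gives 18,000 to 21,000 eligible people, 85–90% of them not on AID in 2023. That is 0.85×18,000 = 15,300 to 0.90×21,000 = 18,900 people, against about 500 Hub starts a year, or roughly 3%. How many will be referred is not known, so this shows only that capacity could bind.

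**What shrinks the bias.**

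- *Window.* Pre-AID years earlier than the look-back have the same expected rate as the period after start. With four pre-AID years, two of them in the look-back, a ratio of 0.65 becomes 1/(0.5/0.65 + 0.5) = 0.79. Time between referral and AID start lies outside the scored period.
- *Overlap.* Counted admissions that the referral form does not capture earn no point and pull the ratio towards 1. If all counted admissions are captured and are a random share of scored episodes, that share cancels and the ratio is unchanged.

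**Death.** Pre-AID deaths are 0. Over the 12-week Hub follow-up, 500 people contribute 500×12/52 = 115 person-years. At an assumed mortality of 0.002 to 0.01 per year, 0.23 to 1.15 deaths are expected. The after/before ratio is infinite with any death and not estimable with none.

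**Non-study controls.** Set against Table 2, the adjustment set covers ethnicity (2 points) and age (1 point), which is 3 of the listed 10. It omits HbA1c, rurality, prior severe hypoglycaemia, complications and occupation.

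**The case against.** The strongest reply is that the size is unknown. Event rates, heterogeneity and selection strength are not in the article. Severe hypoglycaemia is one point of a listed 10, and nearly everyone with type 1 diabetes is eligible in principle. Table 2 does not define the scored event, while Intervention safety counts admissions. The pre-AID window may be set in a fuller document, and referral-to-start time would fit the present wording. Study population also provides for individual review after a recent acute event, and for referral elsewhere first when other active illness is present. Both could offset the selection. All of this stands as a limit on magnitude, so 0.4 to 0.8 is an illustration and not an expected effect.

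It can also be said that zero deaths before start is obvious, and that two of the three comparators can have deaths. That is fair, but the text applies one comparison to all events and exempts none.

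A reader might infer that every before/after ratio is biased. The documents do not support that. DKA and hyperglycaemia admissions earn no points and could be affected only indirectly through the HbA1c points, which has not been quantified.

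A reader might also infer that the non-study contrast must make the Hub look unsafe. Selecting people at higher risk would tend that way, but deferring unwell people pulls the other way, and no figure settles the balance.

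Nor is missing HbA1c adjustment simply an oversight: Statistical analysis says national laboratory data are not available for people outside the study.

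**Conclusion.** The point holds in a limited form.

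- For death, the own-control contrast cannot be made. This needs no assumption.
- For severe hypoglycaemia, upward selection of the pre-AID rate follows from the scoring and invitation rules, and the stated adjustment does not remove it. The ratio of about 0.4 to 0.8 under no effect rests on assumed rates, heterogeneity and selection strength, a pre-AID period within the look-back, and full capture of counted admissions by the scored item. It moves towards 1 as these are relaxed.
- For non-study controls, confounding by the unadjusted score items remains, with net direction and size not established.

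Safety is listed as a secondary outcome, the own-control contrast is one of three comparators, and no decision rule depends on it. This is a should-fix.

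**What to change.** Amend the safety paragraph of Statistical analysis as follows.

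1. Compare death only with non-study controls.
2. For severe hypoglycaemia, limit own-control person-time to the interval from referral to AID start. Otherwise drop that contrast, or label it descriptive with the selection stated.
3. Report each event type separately instead of relying on a pooled SAE rate.
4. In the non-study comparison, add the score items that national records hold: rurality, prior admission for severe hypoglycaemia or DKA, and complication-coded admissions. Their availability in the extract should be confirmed.
5. State that HbA1c remains unadjusted because national laboratory data are not available for non-study people, so residual confounding is expected.

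The cost is analysis wording and a few more administrative fields. The main loss is own-control person-time for severe hypoglycaemia, which may be short for people invited quickly. Recruitment and participant procedures do not change.
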